#### Smartphones as a new way to monitor treatment effects in research

We include smartphone-based self-assessment of mood instability as the primary outcome measure in the RCT for relatives. Similarly, we include data on mood instability for patients with BD. During the last ten years, we have developed and tested a unique smartphone-based system, the Monsenso system for monitoring, diagnosing, and treating BD. Digital electronic and remote self-monitoring of mood offers the possibility of ecological momentary assessments (EMA) [65, 66] for fine-grained real-time assessment in research settings. EMA reduces retrospective recall bias which is a particular problem for mood monitoring because patients need to recall both variation and intensity around a global mean [65]. Moreover, smartphone-based mood ratings in the Monsenso system correlate highly with clinical ratings of mood according to sub-item 1 on the Hamilton Depression Rating Scale 17-items (HAMD-17) and the Young Mania Rating Scale (YMRS), respectively (*p*’s < 0.0001) [67].

The Monsenso system collects time series consisting of data representing daily self-monitoring of mood, activity, sleep, irritability, cognitive problems, alcohol consumption, stress, and medication self-administration. In the version for relatives, medication administration is not included, instead, they are asked to what degree they have supported the patient and if the patient’s BD has been a burden today. Patients and relatives are prompted every evening to fill in these data. The process.

takes 2 min and we have previously shown that adherence to reporting is over 93% during a 6-month trial period [68] and over 72% during a 9-month trial period [69]**.** Besides self-reported data, we will collect daily *automatically* generated smartphone sensor data on physical [37], and social activity [38] that we have shown reflect illness activity.

#### Mood instability—a sensitive primary outcome measure in randomized controlled trials

We have selected mood instability as the primary outcome measure in the RCT as this has several advantages: mood instability has internal validity as a real-life measure for patients and high external validity as it reflects patients’ illness severity and functioning. Extensive evidence shows that mood stability is of core pathogenetic significance in BD [67, 70–73]. Thus, a substantial proportion of patients with BD and relatives experience subsyndromal daily mood swings that are associated with increased perceived stress, decreased quality of life and functioning [67, 73], and increased risk of relapse and hospitalization for patients [70–72]. Increased mood instability behaves as a genetic vulnerability trait for BD as it is present in remitted patients [73] and their unaffected relatives [67]. Accordingly, during the last decade, there has been a gradual shift from a focus on affective episodes to inter-episodic mood instability [74, 75]. Mood instability is currently considered a new treatment target in BD as it appears to be a more sensitive measure of outcome in RCTs than more conventional outcomes focusing on relapse or recurrence of affective episodes [74–76].

### Participant timeline {13}

The participant timeline is shown in Fig. 1.

### Sample size {14}

According to prior analyses [73] mood instability in patients with BD varies on a scale from close to 0 to 10 with an average of 4.1 (SD = 2.6). Our power calculation is based on the assumption that group-based psychoeducation will be associated with a minimum decrease of 0.2 in mood instability compared to the placebo arm; for a power of 80% and a type 1 error risk of 0.05, we need to randomize a total of 126 patients (www.sample-size.net). Also, we need to adjust for situations where one patient has two involved relatives, making them interdependent (estimated to be 30%), and consider expected dropout (estimated to be 10%, as in our prior study [68]) resulting in a total sample size of 180. We expect 200 relatives to agree in participating in the RCT.

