#### Estimation of mood instability

Estimates of instability will be based on readings obtained via the Monsenso system. Relatives and patients score their daily mood on a 9-point scale (patients on a scale from − 3 to + 3 and relatives on a scale 0–8). For each participant, a mood instability measure will be estimated for each day and aggregated in accordance with prior definitions by applying the root mean square successive difference (rMSSD) method [78–80]. The daily mood instability measures, reflecting the extent to which a daily and the previous day’s scores of self-monitored mood differ from one another during follow-up, will be computed as the squared successive difference (SSD) of the reported values. Consequently, daily instability measures can only be computed when consecutive daily values are present. The resulting SSD values are aggregated for each participant as the root mean square successive difference (rMSSD), taking the square root of the mean of the SSD values [80–83]. The instability measures will be computed following the original definition of the rMSSD score. The differences are squared such that positive and negative differences do not cancel out when the values are aggregated by computing the mean. Squaring the values also puts more weight on larger differences. Finally, the square root of the mean puts the aggregated value back on the original scale.

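### The stated 126 does not follow from the stated inputs: a difference of 0.2 with SD 2.6 needs about 5,306, so the claim of 80% power for 0.2 is unsupported and the actual power is unknown

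*Protocol article*

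**What the plan says.** The section Sample size {14} of the protocol article sets out the whole calculation. It reports from prior analyses that "mood instability in patients with BD varies on a scale from close to 0 to 10 with an average of 4.1 (SD = 2.6"). Its target and error rates are stated together as "minimum decrease of 0.2 in mood instability compared to the placebo arm; for a power of 80% and a type 1 error risk of 0.05". From these it concludes that "we need to randomize a total of 126 patients", naming a web calculator. It then allows 30% for relatives who share a patient and 10% for dropout, which gives 180, and expects 200 relatives to take part. No other SD, standardized effect, correlation or sidedness is given.

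The section Outcomes {12} makes mood instability in relatives the primary outcome. The section Estimation of mood instability defines it as the root mean square successive difference (rMSSD) of daily ratings: "Relatives and patients score their daily mood on a 9-point scale", with patients rating from −3 to +3 and relatives from 0 to 8.

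**The concern.** A difference of 0.2 against an SD of 2.6 is 0.077 SD. A difference that small cannot be detected with 80% power by 63 people per arm, so at least one of the three figures (0.2, 2.6, 126) is not what was used or is wrong.

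There is a second problem with the same inputs. They describe patients, while the trial tests relatives, and the quoted range does not fit the outcome as the article defines it.

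What is at stake is how the primary result can be interpreted. The stated power is the design's only account of how small an effect the trial can detect. If it cannot be relied on, neither a null result nor a wide interval can be set against the target of 0.2.

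**Working it through.** **Inputs.** From {14}: difference δ = 0.2, SD σ = 2.6, power 80%, α = 0.05, stated total 126. From Trial design {8}: 1:1 allocation. Sidedness is not stated; two-sided is assumed first.

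**Attempt to reproduce 126.** For two means, n per arm = 2 (z₁₋α/₂ + z₁₋β)² (σ/δ)².

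- 2 × (1.960 + 0.8416)² × (2.6/0.2)² = 2 × 7.849 × 169 = 2,653 per arm, **5,306 in total** (5,308 with the t distribution).
- This is 5,306/126 ≈ 42 times the stated figure, before the protocol's own inflation.

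Other readings of the stated inputs:

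| Reading | Total needed |
|---|---|
| Two-sample, one-sided α | 4,180 |
| Paired or one-sample, two-sided (one-sided) | 1,327 (1,045) |
| 0.2 read as 0.2 SD, two-sided (one-sided) | 786 (620) |
| 0.2 read as 0.2 SD, paired, two-sided (one-sided) | 197 (155) |
| 0.2 read as a 20% fall from 4.1 (0.82 points), two-sided (one-sided) | 316 (250) |
| The same 20% fall, paired | 79 |

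None gives 126. If 126 were per arm, the detectable difference at SD 2.6 would be 0.92, not 0.2.

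**What 126 corresponds to.** With a standardized difference of 0.5, 2 × 7.849/0.25 = 62.8, so 63 per arm and 126 in total. That is either of these:

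- δ = 0.5 × 2.6 = 1.3 points at SD 2.6; or
- δ = 0.2 points at SD = 0.2/(2.8016 × √(2/63)) = 0.40.

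**The later step reproduces.** 126 × 1.3 × 1.1 = 180.2, so the fault lies in the base figure, not in the inflation to 180.

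**Power for 0.2 if SD 2.6 applies.** With 63 per arm, SE = 2.6 × √(2/63) = 0.463 and 0.2/0.463 = 0.432. Two-sided power = Φ(0.432 − 1.960) + Φ(−0.432 − 1.960) = 0.063 + 0.008 = 0.072 (0.071 with the t distribution). The table treats all participants as independent.

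| Total analysed | Power for 0.2, two-sided (t) | One-sided | Difference detectable at 80% power |
|---|---|---|---|
| 126 | 7.1% | 11.3% | 1.30 |
| 180 | 8.1% | 13.0% | 1.09 |
| 200 | 8.4% | 13.6% | 1.03 |

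**Scale check.** If the mood scale has range R, each successive difference is at most R, each squared difference at most R², their mean at most R², and its root at most R. So rMSSD cannot exceed 8 for relatives (0 to 8), or 6 for patients (−3 to +3). A quantity that "varies on a scale from close to 0 to 10 with an average of 4.1 (SD = 2.6") is not shown to be on either scale.

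**The case against.** The strongest reply is that the two halves of the concern pull against each other. If 2.6 belongs to patients on another scale, it cannot establish this trial's power. An SD of about 0.40 for relatives' rMSSD would make 126 correct for 0.2, and the article does not say outright that 2.6 was entered in the calculator. This stands, and it limits the conclusion. A reader might infer that the trial has 7% power. The documents do not support that without the condition that SD 2.6 applies.

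Other inferences also go further than the documents allow:

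- **That covariate adjustment settles the matter.** Bringing 5,306 down to 126 by adjustment would need 1 − 126/5,306 = 97.6% of the variance explained, a correlation of about 0.99. That rules out adjustment as a route from SD 2.6. It says nothing about a smaller raw SD in relatives.
- **That the 0-to-10 figure is itself an error.** It comes from a cited prior analysis that is not at hand, and {14} does not say which mood scale or instability statistic was used there. What can be said is that the input is not shown to be on the outcome's scale.
- **That dropout has already taken the trial below 126.** Trial status gives 25 dropouts among 185, or 13.5%, and 160/1.3 = 123. But that is a count from January 2024 with recruitment still open. At the same rate, 200 relatives give 200 × (160/185)/1.3 ≈ 133. Dropouts with consecutive ratings can also contribute to the mixed model.
- **That the sponsor designed for a standardized difference of 0.5.** This is a back-calculation; the article states neither 0.5 nor 1.3 points.
- **That a null result will be taken to exclude 0.2.** The article proposes no such reading.

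None of this reconciles 0.2, 2.6 and 126. Nor is this detail that an article leaves to a fuller document: {14} gives the calculation, and its figures disagree.

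**Conclusion.** Wrong as written. The sample size section contradicts itself: its stated difference, SD, power and α require about 5,306 in total (4,180 one-sided), not 126, and no standard variant tried recovers 126.

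The size of the shortfall depends on the SD. On the only SD the protocol gives, the trial has about 7 to 8% two-sided power for 0.2 at 126 to 200 relatives. The difference it could detect with 80% power is then about five to six times the stated minimum. Because that SD describes patients on a range the primary outcome cannot reach, the firm conclusion is narrower: 80% power for 0.2 has no support in the document, and the actual power is unknown. These figures assume independent participants and a simple comparison of two means. Choosing a one-sided test does not change the conclusion.

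**What to change.** In {14}, state the SD and the effect actually entered in the calculator, the population and scale they come from, and the sidedness, and correct whichever figure is inconsistent. Unless an SD of about 0.40 for rMSSD in relatives can be documented, replace the power claim for 0.2 with a statement such as: *126 independent analysable relatives give 80% power for a standardized difference of 0.5 (1.3 points if SD = 2.6).*

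Before unblinding, compute the pooled, arm-blinded SD of relatives' rMSSD on the 0–8 scale from the app data. Report the difference detectable at 80% power for the final number, the observed dropout and the clustering of relatives within patients. This fits the blinded analysis already planned under {17b}.

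Recruitment can proceed as planned; the correction needs no extra enrolment. The cost is one corrected paragraph and one blinded calculation, and the stated detectable effect may become less favourable.

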### Trial design {8}

The trial is designed as a two-arm, parallel-group, superiority, randomized trial with a balanced randomization 1:1 to group-based psychoeducation versus a waiting list [38]. The control waiting list group will be offered participation in group-based psychoeducation (active intervention) during the following half year. The trial is planned and will be conducted in concordance with the CONSORT 2010 Explanation and Elaboration: updated guidelines for reporting parallel group randomized trials [39].

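### Sample size {14}: a decrease of 0.2, an SD of 2.6, 80% power and alpha 0.05 cannot all be right together with a total of 126

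*Protocol article*

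**What the plan says.** Everything needed for the calculation stands in the protocol article under Sample size {14} and Trial design {8}.

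- Variability: "mood instability in patients with BD varies on a scale from close to 0 to 10 with an average of 4.1 (SD = 2.6", taken from prior analyses. This is the only SD given.
- Effect: "a minimum decrease of 0.2 in mood instability compared to the placebo arm".
- Design: "two-arm, parallel-group, superiority, randomized trial with a balanced randomization 1:1".
- Error rates and result: "for a power of 80% and a type 1 error risk of 0.05, we need to randomize a total of 126 patients", from an online calculator. Whether the test is one- or two-sided is not said. The 126 is then raised to 180 for relatives who share a patient (30%) and for dropout (10%), with 200 expected to take part.

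Under Estimation of mood instability, the outcome is defined as rMSSD computed from daily mood scores. Relatives score on 0 to 8 and patients on −3 to +3.

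**The concern.** An effect of 0.2 against an SD of 2.6 is a standardised difference of 0.2/2.6 = 0.077, which is very small. A total of 126 is far too few for 80% power at that size. The effect, the SD, the error rates and the answer are all printed in one paragraph, so this is a contradiction between stated figures and not a detail left to another document.

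This paragraph is the article's only justification for the size of the trial, and it concerns the primary outcome. The later figure of 180 is built on 126, so whatever is wrong with 126 carries forward. As printed, nobody can tell which difference in mood instability the trial was sized to detect.

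**Working it through.** **Inputs.** Difference 0.2, SD 2.6, mean 4.1, alpha 0.05, power 80%, total 126 (all Sample size {14}); two arms 1:1 (Trial design {8}). Assumption: two-sided test, with one-sided also tried. Observations are treated as independent.

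**1. What 126 corresponds to.** With n per arm = 2(z₁₋α/₂ + z₁₋β)² / d², where d is the standardised difference:

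2(1.960 + 0.842)² / 0.5² = 62.8, rounded up to 63 per arm, **126 in total**.

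So 126 is reproduced by d = 0.5. In raw units:

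- with SD 2.6, the difference is 0.5 × 2.6 = 1.3, which is 1.3/4.1 = 32% of the quoted mean;
- with a difference of 0.2, the SD is 0.2/0.5 = 0.40 (0.401 when solved for exactly 63 per arm).

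Neither 1.3 nor 0.40 is in the article.

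**2. What the printed inputs need.** n per arm = 2(z₁₋α/₂ + z₁₋β)² SD² / difference²:

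- two-sided: 2(1.960 + 0.842)² × 2.6² / 0.2² = 2,653 per arm, **5,306 in total** (5,308 with the noncentral t);
- one-sided: 2(1.645 + 0.842)² × 2.6² / 0.2² = 2,090 per arm, 4,180 in total.

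**3. Other readings of the same figures.** None gives 126.

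| Reading | Total for 80% power |
|---|---|
| 0.2 as a standardised difference, two-sided | 786 |
| 0.2 as 20% of the mean (0.2 × 4.1 = 0.82), SD 2.6, two-sided | 316 |
| The same, one-sided | 250 |
| 2.6 as a variance, two-sided | 2,042 |
| Paired design, SD of differences 2.6, two-sided | 1,327 |

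Baseline adjustment would have to shrink the variance by the factor 126/5,306 = 0.0237, which needs a correlation of √(1 − 0.0237) = 0.988. The model under Statistical methods {20a} names only a fixed effect of group and a person-specific random effect.

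**4. Power and detectable difference on the printed inputs** (two-sided t-test, SD 2.6, before clustering and dropout). At 126 the standard error is 2.6 × √(2/63) = 0.463, so the expected test statistic is 0.2/0.463 = 0.43 against a critical value near 1.96. Detectable difference = (1.960 + 0.842) × 2.6 × √(4/N).

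| Total N | Power for 0.2 | Difference detectable with 80% power |
|---|---|---|
| 126 | 7.1% | 1.30 |
| 180 | 8.1% | 1.09 |
| 200 | 8.4% | 1.03 |

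**5. Dependence on the SD.** These SDs are assumptions, since the article gives none for relatives.

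| Assumed SD | Power for 0.2 at N = 126, two-sided |
|---|---|
| 0.40 | 80% |
| 0.6 | 46% |
| 1.0 | 20% |
| 2.6 (printed, patients) | 7% |

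**The case against.** The strongest reply is that the article never says 2.6 was the SD entered in the calculator. It appears as background on patients, from earlier work. It also cannot belong to the trial's endpoint as defined: no successive difference in relatives' mood can exceed 8, nor in patients' mood 6, so rMSSD cannot exceed those values, whereas the quoted metric runs to 10. The effect of 0.2 may therefore have been meant on another scale with another SD, and an SD of 0.40 would make 126 exactly right.

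This stands, and it limits the conclusion. A reader might infer from the arithmetic that the trial has about 7% power, or that the claimed power does not exist. The article does not support that: 7% holds only if 0.2 and 2.6 share a scale and 2.6 applies to relatives. The reply does not rescue the paragraph, however. It offers 2.6 as its only SD, and reaching 126 takes one 6.5 times smaller (2.6/0.40) that is neither stated nor sourced. Unstated sidedness does not help either, since the one-sided total is 4,180.

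Two further inferences should be resisted.

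- The step from 126 to 180 might look wrong as well. But 126 × 1.3 × 1.1 = 180.2 and 126/0.7 = 180 both give the printed figure, and the article does not show its chain, so no error is established there.
- A reader might assume that a non-significant result would be presented as proof of no effect. Nothing in the article says so.

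**Conclusion.** The paragraph is wrong as written: the effect, the SD, the error rates and the total of 126 are mutually inconsistent. The gap is large, at 126 against about 5,306 (two-sided assumed), or equivalently a detectable difference of 1.30 against the stated 0.2. That comparison rests on a simple two-mean test with independent observations and on taking 0.2 and 2.6 as being on one scale, as the paragraph presents them. Allowing for clustering and dropout would lower power further.

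What cannot be concluded is the trial's actual power for the relatives' rMSSD. It depends on an SD in relatives that the article does not give, and over the SDs examined power for 0.2 at 126 runs from 80% down to about 7%.

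**What to change.** Correct Sample size {14} without changing enrolment:

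- State the effect, the SD and the sidedness actually used, with a source for the SD in relatives on the rMSSD scale that will be analysed.
- Restate the size as 126 independent relatives giving 80% power for a standardised difference of 0.5 (two-sided 0.05, if that was the test).
- If 2.6 was the SD used, say that the difference detectable at 126 is about 1.3 and that power for 0.2 is about 7%.
- If 0.2 stays as the target, state and source the SD of about 0.40 that makes 126 correct.

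The cost is one rewritten paragraph and, unless an SD near 0.40 can be sourced, a less favourable power statement. No extra participants are needed.

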### Recruitment {15}

Patients at Copenhagen Affective Disorder Clinical are routinely informed about the possibility of psychoeducation for their relatives. If interested, the patients will hand in a registration form with the name and phone numbers of their relative(s). The clinic generally recommends that patients start in psychoeducational group therapy themselves before their relatives are enrolled in psychoeducation. This is however only a recommendation and not a rule. Relatives’ psychoeducation groups are offered once in the autumn and two during spring.

Data from patients with BD are collected from the A-bipolar study, which is a parallel ongoing study [42]. We will secure written consent from the participants in the A-bipolar study to utilize their data in the R-bipolar study.

## Assignment of interventions: allocation

### Sequence generation {16a}

On the webpage www.randomization.com, we produced a randomization plan. The random numbers allocated the participants in either intervention (1) or control group (2).

We chose to have block randomization to achieve equal sizes of the groups during the ongoing recruitment process. If two participants were related to the same patient, they would be grouped together, as they would not be independent participants.

### Concealment mechanism {16b}

The randomization plan was downloaded as an Excel File, converted to a CSV file, and then uploaded to RedCap (https://www.project-redcap.org/). In RedCap a randomization module was set up, using the uploaded randomization plan.

### Implementation {16c}

JRS and MFJ generated the randomization plan. JRS enrolled the participants and assigned participants to intervention or control groups at the end of each inclusion visit.

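### Concealment from the enroller is not assured, and a relative enrolled after another relative of the same patient has an arm already fixed before consent and T0

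*Protocol article*

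**What the plan says.** Four sections of the Protocol article bear on this point.

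- **Sequence generation {16a}.** "We chose to have block randomization to achieve equal sizes of the groups during the ongoing recruitment process". No block size is given. For families the rule is: "If two participants were related to the same patient, they would be grouped together, as they would not be independent participants". Nothing is said here about when a second relative is seen.
- **Concealment mechanism {16b}.** The path of the file is given first: "The randomization plan was downloaded as an Excel File, converted to a CSV file, and then uploaded to RedCap". The section then turns to the tool used for allocation: "In RedCap a randomization module was set up, using the uploaded randomization plan". It does not say who handled the file or who could still open it after upload.
- **Implementation {16c}.** Two investigators "generated the randomization plan". One of the two also "enrolled the participants and assigned participants to intervention or control groups at the end of each inclusion visit".
- **Who will be blinded {17a}.** Participants and this investigator are unblinded. The stated protection is that allocation closes the inclusion visit, so that baseline questionnaires and ratings are already done.

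Under {26a} and {18a} the same investigator phones the relatives, takes most consents and does nearly all the assessments.

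**The concern.** Concealment requires that whoever decides if and when a person enters the trial cannot know the next arm. Two features of this plan leave that open.

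The first is the overlap of roles. One person co-generated the sequence, approaches relatives, takes consent and carries out the allocation.

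The second is the family rule, which matters whoever holds the list. Once the first relative is allocated, the arm of any relative of that patient who enters later is settled. The unblinded enroller and the unblinded first relative can both know it.

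The comparator is a waiting list, so a relative who knows that waiting lies ahead may decline or delay, and this would happen in one arm only. That kind of selection would reach the primary outcome, which participants report themselves and which no later blinding protects. Blinded analysis ({17b}) does not repair differences in who entered. A smaller effect concerns baseline interviews: for later relatives the interviewer could rate HAM-D6, YMRS and FAST knowing the arm. Those are secondary outcomes. The app-based primary outcome is not rated by the interviewer.

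**Working it through.** The plan states no figure for concealment, so there is none to reproduce. The check sets the sections side by side and then sizes the reach.

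**1. Role overlap.** {16c} names the enroller as one of two people who generated the list. {16b} offers a database module fed with that list. A module conceals a sequence from users who have not seen it. It cannot do so for a person who produced it, unless access was later removed or the list was regenerated by someone else, and the article states neither.

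**2. Family rule against the timing safeguard.**
- {16a}: relatives of one patient go to the same arm.
- {16c}: allocation is made visit by visit, when each inclusion visit closes.
- {17a}: baseline data are therefore collected before allocation.

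For a relative included at a later visit than the first, the first two statements fix the arm before consent and T0. The third then does not hold for that person. It does hold for relatives included together at one visit, but the article describes no joint visits and no allocation by family.

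**3. How many relatives.** Inputs from Sample size {14}: 30% for patients with two involved relatives (the unit, patients or relatives, is not clear) and 200 relatives expected. Assumption: at most two relatives per patient.

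| Reading of 30% | Share who are second relatives | Of 200 |
|---|---|---|
| 30% of relatives are in pairs | 0.30 / 2 = 0.15 | 0.15 × 200 = 30 |
| 30% of patients bring two relatives | 0.30 / 1.30 = 0.231 | 0.231 × 200 ≈ 46 |

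Both are upper limits for their reading, because jointly included pairs drop out of the count.

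**4. Predictability without the list (illustration).** Block sizes 2 to 8 are an assumption. In permuted 1:1 blocks of fixed size b, someone who knows b and the past allocations is certain of a share 1/(b/2 + 1) of assignments:
- b = 2: 1/2 = 50%
- b = 4: 1/3 = 33%
- b = 6: 1/4 = 25%
- b = 8: 1/5 = 20%

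A simulation of 100,000 blocks per size agreed (50%, 33%, 25%, 20%). With the generated list in hand, every assignment could be known.

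**The case against.** The strongest reply is that the article never says the arm was visible. It names a randomization module and places allocation after baseline. Its account of the file is in the passive voice, so it does not say that the enroller downloaded or kept it. Access rights are a detail that an article may leave to the full protocol. This stands as far as it goes: a reader might infer that allocation was openly unconcealed or that the enroller worked from a spreadsheet, and the documents do not support either. What they do state is that the enroller co-generated the sequence, and that is enough to say concealment from that person is not assured.

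Second, the article gives no timing for relatives of one patient. According to Recruitment {15}, the patient hands in a form that can name more than one relative, which is compatible with joint inclusion. So it cannot be said that every second relative entered with a known arm, nor that the first relative told the second. The point is limited to those enrolled at a later visit, for whom the arm was fixed and knowable.

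Third, knowledge of the arm at the baseline interview might be read as biasing the primary outcome. It does not do so directly, since that outcome is self-reported in the app. Only selective entry could affect it.

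Fourth, the time to change enrolment has almost passed. Trial status reports 185 relatives included by 5 January 2024 and expects recruitment to end that month, so at most about 200 − 185 = 15 of the expected relatives remained. That limits what can be done prospectively, but it does not affect the analysis or the reporting.

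**Conclusion.** The point holds in limited form. Concealment from the enroller is not assured, because list generation, enrolment and assignment meet in one person and the module cannot undo that. Independently, the baseline-before-allocation safeguard in {17a} fails for any relative enrolled at a later visit than the first relative of the same patient.

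The second route could touch about 15% to 23% of relatives (30 to 46 of 200). The range reflects the unclear unit of the 30% in {14}; it assumes no more than two relatives per patient and separate visits, and it shrinks with every joint inclusion. The role overlap cannot be sized, because the article does not state list access or block size.

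A reader might conclude that selection bias occurred. The text shows only that selective enrolment was possible.

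**What to change.** 1. **Before unblinding, prespecify a sensitivity analysis** of the primary outcome restricted to the first-enrolled relative of each patient. The logbook in Data management {19} already links relatives to patients; order of entry can be taken from inclusion or consent dates, assuming these were recorded. The cost is one extra model and about 15% to 23% fewer relatives in it (200 − 30 = 170, or 200 − 46 = 154), hence less precision.
2. **Tabulate second relatives and their baseline data by arm.** A clear imbalance in number or baseline would point to selective entry. This needs no new data.
3. **Correct {16b} and {17a}.** State who had access to the list and when, and that T0 did not precede allocation for later-enrolled relatives. This is a matter of wording.
4. **For any enrolment still open,** complete consent and T0 for all relatives of a patient before that patient's single allocation. With recruitment nearly over, this can affect few or no participants.

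Item 1 deals only with the second-relative route. It does nothing about an enroller who may know the sequence, so the overlap of roles should be reported as a limitation.
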